### **3.6 Anesthesia protocol**

#### **3.6.1 Preoperative management**

On the day of surgery, shortly before going to the operating room, patients' cognition was assessed using the Montreal Cognitive Assessment (MoCA). After participants entered the operating room, indwelling needle was used to establish intravenous channels. Then lactate Ringer's solution was injected, and vital signs were monitored, including (1) ECG; (2) Non-invasive blood pressure and invasive blood pressure monitoring; (3) Pulse oxygen saturation (SpO2); (4) Nasopharyngeal temperature; (5) Bispectral index (BIS). The baseline values of all monitoring indicators of the patient are recorded after the patient is stabilized (systolic and diastolic blood pressure and heart rate are the basic values at this time).

#### **3.6.2 Protocol of anesthesia**

All participants were given routine general anaesthesia induced with etomidate and maintained with sevoflurane in oxygen/air, propofol, fentanyl, and muscle relaxants. BIS was used to monitor the depth of anesthesia, and maintained at 45-60. Neuromuscular block was provided with continuous intravenous infusions or intermittent boluses of cisatracurium. Benzodiazepines, ketamine, and dexmedetomidine were avoided to the extent practical, with other aspects of anaesthetic management left to clinicians' discretion. Blinded investigators reviewed all electronic anaesthesia records to confirm protocol compliance and collect intraoperative data.

#### **3.6.3 Airway management**

After patient's eyelash reflex disappeared, muscle relaxation was complete and BIS was stable at 45-60, endotracheal intubation was completed. The volume control ventilation mode is adopted during surgery. The tidal volume was set to 6-8 ml/kg, and respiratory frequency was set to 10-12 times/min. PETCO2 was maintained at 35~45 mmHg.

### **3.7. Outcome measures**

#### **3.7.1 Preoperative measures**

(1) Demographic information: age, sex, height, weight, body mass index, education level, cognition;

- (2) Medical history: past history, history of anesthesia, ASA classification, comorbidities, diagnoses;
- (3) Procedure: type of procedure;
- (4) Circulatory indicators: pre-anesthesia vital signs (heart rate, [HR], systolic BP [SBP], diastolic BP [DBP], SpO2, respiratory rate [RR]);
- (5) Laboratory examination: Blood routine examination, liver and kidney function;
- (6) Mental state: used by Geriatric depression scale;
- (7) Preoperative cognitive function status: used by Montreal Cognitive Assessment (MoCA); [41]
- (8) Presence of delirium before surgery: used by Confusion Assessment Method (CAM);[42]
- (9) Preoperative frailty: used by the Frail Scale.

### **3.7.2 Intraoperative measures**

- (1) The use of anesthetic drugs and vasoactive agents;
- (2) intraoperative fluid balance;
- (3) Dosage of Midazolam;
- (4) Dosage of Dexmedetomidine;
- (5) Surgical procedures (with cardiopulmonary bypass or without);
- (6) No. of distal anastomosis;
- (7) Length of surgery;
- (8) Length of anesthesia;
- (9) Hemodynamic information: (heart rate, [HR], mean arterial pressure (MAP), central venous pressure (CVP) systolic BP [SBP], diastolic BP [DBP], SpO2, respiratory rate [RR], BIS value, ETCO2).

All intraoperative data were obtained by review of medical records and anesthesia records.

### **3.7.3 Postoperative outcomes**

#### **The primary outcome:**

The incidence of delirium from postoperative day 1 to postoperative day 7 or before discharge, whichever occurred first.

Diagnosis of POD was based on the results of CAM or CAM-ICU twice daily, [42,43] specifically from 08:00 to 10:00 and from 18:00 to 20:00. All blinded researchers were trained in CAM/CAM-ICU assessment and the consistency among research members was reached. When there is a contradiction between the diagnosis obtained by the scale and the diagnosis of the psychiatrist, when there are still differences after consultation, the diagnosis of the psychiatrist shall prevail. In order to prevent missed diagnosis, we should communicate with the medical staff in the ward in time. After the patient is selected, the family member or escort staff should be informed, and the investigator should be informed of the evaluation of delirium in time when any abnormal performance of the patient's mood, consciousness, cognition and so on is found. Comprehensive reviews of progress notes, nursing documents, and medical records were conducted by blinded investigators to identify instances of delirium between postoperative day 1 and 7, employing a chart-based delirium identification instrument. [44,45] Patients diagnosed with delirium through any of the aforementioned methods were considered to have experienced delirium on that particular day. When postoperative delirium is found, the subject should communicate with the competent physician and decide on further diagnosis and treatment. If the patient's performance was normal 7 d after operation, the visit ended, while the patient with continuous delirium was followed up

until normal or discharged.

Outcomes were assessed by investigators specifically trained in recognition and assessment of delirium.

**Secondary outcomes:**

- (1) cumulative incidence of POD
- (2) incidence of severe delirium, evaluated with the Memorial Delirium Assessment Scale (MDAS)[46]
- (3) postoperative cognitive dysfunction (POCD) on postoperative day 7 or at discharge if earlier, used by the Montreal Cognitive Assessment (MoCA) (range, 0 [worst] to 30 [best]), defined as a 1 standard deviation decrease from baseline in Montreal cognitive assessment score at postoperative day 7 or discharge.
- (4) cognitive function one month after surgery, used by the Revised Telephone Interview for Cognitive Status (TICS-m) (range, 0 [worst] to 50 [best])
- (5) 30-day all-cause mortality
- (6) durations of intensive care unit (number of days in the intensive care unit from the end of operation to discharge) and postoperative hospital care.
- (7) elapsed time from the end of surgery to delirium onset
- (8) duration of delirium (defined as the period between the first and last delirium-positive day, even if there were non-delirious days in between)
- (9) the total number of delirium-positive days in patients who developed delirium
- (10) cognitive function at three time points (baseline, preoperative, postoperative day 7 or at discharge if earlier. was used to assess early POCD on the seventh day after surgery or at discharge and cognitive function at any time points before or after surgery.
- (11) Postoperative intubation time, defined as duration from the end of the procedure to extubation.
- (12) intensive care unit readmission within 30 days after surgery.
- (13) Number of days alive and out of the hospital within 30 days. (The sum of the number of days patients were alive and not in the hospital within 30 days after surgery. It is calculated as 30 days minus the total number of days in hospital after surgery (maximum 30 days, minimum 0 days). If the patient is not hospitalized from 00:00 to 24:00 in a day, the number of days without hospitalization can be counted; After discharge, patients were hospitalized for a second time, and the second hospitalization time was also included in the total number of days in hospital. The patient died within 30 days of surgery. DAOH 30 is 0 days; If the patient was not discharged 30 days after surgery, DAOH 30 was recorded as 0 days.)

All outcomes were assessed by investigators masked to patient allocation.

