#### **General analysis:**

The data analyses mainly include statistical description and statistical inference. Quantitative data will be described by central tendency and dispersion tendency. The normally distributed data of central tendency and dispersion tendency will be described as means and standard division, respectively. The non-normally distributed data of central tendency and dispersion tendency will be described as median and quartiles. The qualitative data will be described as frequency and percentage. Statistical inference,

independent t test or non-parameter test will be used to compare the quantitative data between the two groups, while chi-square test or Fisher's exact test will be used for comparing the qualitative data between the two groups.

For missing data, imputation techniques were used. Statistical analyses were performed using SPSS 23.0 (IBM SPSS) and R (R software 4.2.1), and 2-sided  $P < 0.05$  was considered to be statistically significant in all statistical tests.

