#### **4.2.4 Analysis of primary endpoint**

The incidence of POD between the two groups was compared with  $\chi^2$  tests, and the odds ratio (OR) with 95% CI was calculated.

The time-to-event analytic approach was also used to compare the cumulative incidence of POD between the groups. Kaplan-Meier analysis was used to estimate the cumulative incidence of POD, and difference of incidence between groups was compared with the log-rank test.

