#### **4.2.5 Analysis of other endpoints**

For secondary and exploratory endpoints, continuous data will be presented as means (SDs) or median (IQRs), as appropriate. The secondary endpoint followed no Gaussian distribution, will be presented as median (interquartile range) and tested by Mann-Whitney U test. POCD was defined as a 1 standard deviation decline in MoCA score on postoperative day 7, or at discharge if earlier, compared to baseline. This definition aligns with previous definitions of POCD and current recommendations for defining POCD or delayed neurocognitive recovery. [48,49] Mantel-Haenszel  $\chi^2$  and Cuzick tests assessed a potential dose-response relationship between the total hours of cognitive training and incidence of delirium. Analyses of delirium duration and delirium-positive days were conducted using the Zero-inflated Poisson regression model. Regarding the assessment of delirium severity, ordinal logistic regression model was used to model no delirium, delirium and severe delirium. Additionally, a post-hoc analysis incorporating study site, age, surgical technique, baseline educational level and cognitive function of the participants was conducted.

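### Time to delirium onset is a separate secondary outcome with no method or population of its own; by the default rules it would be tested only among patients who became delirious

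*Protocol*

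**What the plan says.** The secondary outcomes in Protocol section 3.7.3 include "cumulative incidence of POD" as item 1 and, separately, "elapsed time from the end of surgery to delirium onset" as item 7. Item 7 comes with no population and with no value or censoring rule for a patient who never becomes delirious.

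The analysis sections assign methods as follows:

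- Section 4.2.4: "The time-to-event analytic approach was also used to compare the cumulative incidence of POD between the groups", by Kaplan-Meier and log-rank. Item 7 is not named.
- Section 4.2.5: "Analyses of delirium duration and delirium-positive days were conducted using the Zero-inflated Poisson regression model". This covers items 8 and 9. Severity has an ordinal logistic model. Item 7 has no model of its own.
- Section 4.2.3, general analysis: "independent t test or non-parameter test will be used to compare the quantitative data between the two groups".
- Section 4.2.5, for non-normal secondary endpoints: "will be presented as median (interquartile range) and tested by Mann-Whitney U test".

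Section 4.2.3 also sets a two-sided 0.05 threshold for all tests.

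**The concern.** An onset time exists only in a patient who became delirious. A t test or Mann-Whitney test on it can therefore use only those patients, and who they are is decided after randomisation by the primary outcome, which the trial expects training to change. If training prevents some kinds of delirium more than others, the remaining cases in the two arms differ in kind as well as number, and randomisation no longer protects the comparison. If mainly late cases are prevented, onset looks earlier with training and may be read as harm. If mainly early cases are prevented, onset looks later and may be read as a further benefit. Either result could appear with P < 0.05 although training shifted nobody's onset time.

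**Working it through.** **1. Which rule reaches item 7.** Kaplan-Meier and log-rank are tied to item 1, zero-inflated Poisson to items 8 and 9, and the ordinal model to severity. Of the stated rules, only the two defaults (t test or non-parametric test in 4.2.3, Mann-Whitney in 4.2.5) cover an elapsed time. This is an inference from the defaults; the protocol does not name a test for item 7.

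**2. The protocol's own sample size (section 4.1).** Inputs: 35% against 17.5%, two-sided 0.05, 80% power, 10% dropout.

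n = (1.960 + 0.842)² × [0.35 × 0.65 + 0.175 × 0.825] / (0.35 − 0.175)² = 7.849 × 0.371875 / 0.030625 = 95.3, so 96 per group. Then 96 / 0.90 = 106.7, so 107 per group. Both stated figures reproduce.

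**3. Size of the delirious-only comparison.**

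| Patients per group | Control, delirious | Training, delirious |
|---|---|---|
| 96 | 0.35 × 96 = 33.6 | 0.175 × 96 = 16.8 |
| 107 | 0.35 × 107 = 37.5 | 0.175 × 107 = 18.7 |

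At 33.6 against 16.8, 80% power needs a standardised difference of about 2.802 × √(1/33.6 + 1/16.8) = 0.84, so the test is also weak for a real difference.

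**4. Simulation with a vulnerability score.** The assumptions are not in the documents. Each patient has a normal vulnerability score, and in the control arm those above the 65th percentile become delirious. Log onset time correlates with vulnerability at −rho, identically in both arms. Training halves delirium and has no effect on timing. There are 96 patients per arm and 4,000 trials per setting, with Mann-Whitney applied among the delirious. False rejection rates:

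| Who is spared by training | rho = 0.5 | rho = 0.7 | rho = 0.9 |
|---|---|---|---|
| All of the less vulnerable half of cases, none of the rest | 11% | 20% | 50% |
| 65% of the less vulnerable half, 35% of the rest | 5% | 6% | 8% |
| 50% of both | about 5% | about 5% | about 5% |

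At rho = 0 the all-or-none rule also gives about 5%. Repeat runs agree within simulation error; the middle row ranges from 4% to 9%. The mean spurious shift under all-or-none selection is 0.24 to 0.60 SD.

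**5. A second model, to check direction.** Assumed: 70% of control onsets fall at 12–48 h and 30% at 48–168 h, delirium is halved, and no onset is delayed. There are 5,000 trials per row.

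| Early cases prevented | Late cases prevented | Rejection | Median onset with training |
|---|---|---|---|
| 50% | 50% | 4% | no material difference |
| 61% | 25% | 13% | about 12 h later |
| 71% | 0% | 40% | about 32 h later |
| 39% | 75% | 12% | about 4 h earlier |
| 29% | 100% | 39% | about 8 h earlier |

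The selection rule drives the result, and the sign depends on which cases are prevented.

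**The case against.** The strongest reply is that the protocol never says item 7 is tested among delirious patients only. It writes such a restriction where it wants one, in item 9 ("the total number of delirium-positive days in patients who developed delirium"), and not in item 7. The wording of item 7 is that of a time-to-event variable, and section 4.2.4 already plans Kaplan-Meier and log-rank on that same time axis in all analysed patients. If that is the intended analysis of item 7, the selection problem disappears and item 7 simply overlaps with item 1. This reply stands in part: it shows that an invalid test is not expressly planned. It does not settle the matter, because section 4.2.4 names only cumulative incidence and the default rules, applied as written, would still give item 7 its own P value.

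A separate analysis plan might name the method. However, section 4 of this protocol carries the title of a statistical analysis plan and assigns methods to outcomes. The difficulty is what its stated defaults lead to, and not that detail is left for later.

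A reader might go further and infer that training would falsely appear to hasten onset, with error rates up to 50%. The documents do not support that. They say nothing about which cases training would prevent, the high figures need a sharp all-or-none cut-off together with a strong correlation, and the shift can go either way.

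A reader might also extend the point to item 9. That does not follow, because section 4.2.5 gives delirium-positive days a zero-inflated Poisson model, so the Mann-Whitney default does not reach it.

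**Conclusion.** The point holds as a gap in assignment with a foreseeable bad consequence. Item 7 has no stated method or population, and the defaults that reach it would produce a comparison of about 34 with 17 patients that randomisation does not protect. Whether bias would occur depends on an unknown: how far prevention of delirium is related to onset time. With no relation the test keeps roughly its nominal 5%; under mild selection the rate is 4% to 9%; the 11% to 50% range belongs to the extreme assumed selection only. One of 13 secondary outcomes is affected. The primary chi-square analysis, the all-patient log-rank comparison and the sample size are untouched. The change is still worth making because it is specific and nearly free.

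**What to change.** State in section 4.2.5 that item 7 is analysed by the time-to-event approach of section 4.2.4. This should include all modified intention-to-treat patients, counted from the end of surgery, with non-delirious patients censored at day 7 or at discharge if earlier. State explicitly how death before delirium is handled, for example as a competing event. Reconcile this with section 3.2.3, which drops patients who die before the primary outcome assessment, whereas the modified intention-to-treat definition in section 4.2.1 excludes only those with no follow-up record or a cancelled operation. Report onset times among delirious patients descriptively (median and interquartile range) without a P value.

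No new data are needed. The cost is a short addition to 4.2.5, the reconciliation of the rule on deaths, the loss of one P value on about 50 patients (33.6 + 16.8 = 50.4), and an acknowledged overlap between items 7 and 1.

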## **4. Statistical Analysis Plan**

### **4.1 Sample size calculation**

In a previous study of patients recovering from coronary artery bypass graft surgery, the incidence of postoperative delirium was 35%.[47] We powered our trial to detect a 50% relative reduction in delirium from a 35% baseline consequent to cognitive training. 96 patients were required in each group for a two-tailed  $\alpha=0.05$  with 80% power. Assuming a potential dropout rate of 10%, we included a total of 214 patients (107 in each group).

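### Delirium-positive days are defined only in delirious patients, yet the planned zero-inflated Poisson model needs zeros; the population for outcomes 8 and 9 and the day count for outcome 8 must be fixed

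*Protocol*

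**What the plan says.** Four places in the protocol bear on this point.

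- **Section 3.7.3, secondary outcome 9**, counts "the total number of delirium-positive days in patients who developed delirium".
- **Section 3.7.3, secondary outcome 8**, is the "duration of delirium (defined as the period between the first and last delirium-positive day, even if there were non-delirious days in between"). It gives no value for a patient without delirium and does not say whether both end days count.
- **Section 4.2.5** fixes one model for both: "Analyses of delirium duration and delirium-positive days were conducted using the Zero-inflated Poisson regression model". It names no population.
- **The Programme summary** (secondary indicators) lists outcome 9 simply as a count of positive days, without limiting it to patients who became delirious.

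The rule for a positive day stands under the primary outcome: "Patients diagnosed with delirium through any of the aforementioned methods were considered to have experienced delirium on that particular day". Section 4.2.1 assigns the modified intention-to-treat (mITT) set to the primary indicators and names no set for outcomes 8 and 9.

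**The concern.** A zero-inflated Poisson model describes counts with more zeros than a Poisson distribution allows. By the protocol's own rule, a patient who developed delirium has at least one positive day, so the population in outcome 9 contains no zeros. The detailed definition and the stated model cannot both be followed as written.

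The choice between them matters. Becoming delirious is the primary outcome, and training is intended to change it. A comparison among delirious patients only is therefore not a comparison of randomised groups: the delirious patients left in the training arm may differ systematically from those in the control arm. A comparison over all patients, with 0 for no delirium, does not have this problem. As the text stands, an analyst could defend either one.

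**Working it through.** **1. Planning inputs (section 4.1).** The trial is sized as follows: "We powered our trial to detect a 50% relative reduction in delirium from a 35% baseline consequent to cognitive training". The rates are therefore 0.35 and 0.175, with 96 per group, two-sided alpha 0.05 and 80% power. The unpooled formula reproduces the stated size:

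n = (1.960 + 0.842)² × (0.35×0.65 + 0.175×0.825) / 0.175² = 7.85 × 0.3719 / 0.0306 ≈ 95.3, rounded up to 96. Allowing 10% dropout, 96 / 0.9 = 106.7, so 107.

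**2. Patients in each possible population (96 per arm).**

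| | Control | Training | Total |
|---|---|---|---|
| Delirious | 96 × 0.35 = 33.6 | 96 × 0.175 = 16.8 | about 34 + 17 |
| Not delirious | 62.4 | 79.2 | 141.6 of 192 (74%) |

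The delirious-only data set has no zeros. The all-patient data set has about 142.

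**3. The model without zeros.** Let π be the inflation probability. With no zeros, the log-likelihood is n·log(1 − π) plus the ordinary Poisson log-likelihood. It is largest at π = 0, which is minus infinity on the logit scale. The inflation part is then not estimable, and the count part returns the observed group means.

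Simulation agrees. Zero-truncated counts were drawn for 34 and 17 patients, 100 data sets for each of three assumed Poisson rates (0.8, 1.5 and 2.5). The estimated π was below 0.00001 every time, with a median standard error of 68 to 166 on the logit scale. Fitted rates averaged 1.45, 1.93 and 2.70, against truncated means of 1.45, 1.93 and 2.72.

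**4. The model with zeros.** Fitted to all 192 patients, the same model recovers the rates (0.78, 1.51 and 2.44), with control-arm π of 0.35, 0.55 and 0.61. The two arms were given the same day distribution among delirious patients, and the median count-part ratios were 0.95, 1.00 and 0.99. Yet days per patient halve: at rate 1.5, 34 × 1.93 / 96 = 0.68 against 17 × 1.93 / 96 = 0.34. The count part alone would therefore show no effect. The overall mean, (1 − π) × rate, is needed.

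**5. What selection can do.** The protocol gives no distribution of days, so one is assumed for the 34 delirious controls: 14 with one day, 9 with two, 6 with three, 3 with four and 2 with five. The total is 72 days: 72/34 = 2.12 per delirious patient and 72/96 = 0.75 per patient. The 17 shortest episodes (14 × 1 + 3 × 2) hold 20 days and the 17 longest hold 52.

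| Episodes prevented by training | Training: days per delirious patient (control 2.12) | Training: days per patient (control 0.75) |
|---|---|---|
| Shortest 17 | 52/17 = 3.06 | 52/96 = 0.54 |
| Random half | 36/17 = 2.12 | 36/96 = 0.38 |
| Longest 17 | 20/17 = 1.18 | 20/96 = 0.21 |

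Days per patient fall in every row. The delirious-only mean rises, stays the same or falls.

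**6. Outcome 8.** The period is "defined as the period between the first and last delirium-positive day". Read as last minus first, an episode confined to one day scores 0; read inclusively, it scores 1. On the first reading, and with non-delirious patients entered as 0, a one-day delirium cannot be told from none. In the assumed distribution that would be 14 of the 34 delirious controls.

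**The case against.** The strongest reply is that an all-patient analysis was meant. The Programme summary carries no restriction, and a zero-inflated model makes sense only if patients without delirium enter as zeros. On that reading the model can be fitted and the data set is the randomised one, apart from the mITT exclusions. This reply has force: the documents do not establish that the trial will compare non-randomised subsets, only that one of its stated definitions would. It does not remove the conflict. The summary is an abbreviated list, while section 3.7.3 is the detailed definition and says the opposite.

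Three stronger readings are tempting but not supported:

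- *That the model would give a biased ratio in delirious patients.* It returns the observed means, and their ratio is the correct descriptive contrast for outcome 9 as worded. It differs from the ratio of the underlying untruncated rates, but that is not what the outcome defines. Whether software reports convergence depends on the optimiser and says little about the plan.
- *That training would look harmful.* That is one row of a table built on an assumed distribution. The other two rows do not show it.
- *That outcome 8 also has no zeros.* Its wording is not restricted to delirious patients, and an inclusive count is a natural reading. Its defect is ambiguity.

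Nor do the documents call for a different model family. The zero-inflated model works once the zeros are present.

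**Conclusion.** The concern holds as an inconsistency between a stated population and a stated model for outcome 9, together with an undefined day count for outcome 8. If section 3.7.3 is followed, the inflation part has nothing to estimate, and the result is a Poisson comparison of about 34 against 17 patients selected on the primary outcome. That contrast can point the wrong way: against 2.12 days in controls it ranges from 1.18 to 3.06 in the example, while the per-patient mean falls from 0.75 to between 0.21 and 0.54. The patient numbers rest on the planning rates; the day figures rest on the assumed distribution and show only what is possible.

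These are two of thirteen secondary outcomes. The primary analysis and the sample size are unaffected. The text should nevertheless be corrected, because the choice of population can change the direction of the reported result.

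**What to change.** 1. Define outcomes 8 and 9 in all mITT patients, with 0 for a patient without delirium, and use the same wording in the Programme summary, section 3.7.3 and section 4.2.5.
2. Define duration as last minus first positive day plus 1, so that a one-day episode scores 1.
3. Keep the zero-inflated Poisson model, or use a hurdle model, but report the overall effect per patient (the ratio of overall means) and not the count part alone.
4. Show days among delirious patients descriptively, labelled as a subset formed after randomisation.

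The cost is the wording of two secondary outcomes and one sentence of the analysis section. No extra data collection or sample size change is needed.
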